**7**. **Refugees around the World:**

Refugees has been defined by the 1951 ‘United Nations Convention on Refugees’ as people with “a well-founded fear of being persecuted for reasons of race, religion, nationality, membership of a particular social group or political opinion, is outside the country of his nationality, and is unable to, or owing to such fear, is unwilling to avail himself of the protection of that country”^[[4]](#footnote-4)^. This definition has been used in all international laws and by international standards (Bates, 2002). Refugees have to travel in order to save their lives or maintain their freedom because they have no security in their own countries; thence, if other countries do not let them in, and do not help them once they are in, then they may be judging them to death or to an unbearable life, without rights.^[[5]](#footnote-5)^

At the end of 2014, 19.5 million refugees were found worldwide with a 51% of them were under 18 years old. According to United Nations High Commissioner for Refugees (UNHCR) 2016, an average of 42,500 persons per day were forced to leave their homes and seek protection elsewhere, either within the borders of their countries or in other countries^[[6]](#footnote-6)^. Moreover, it has been estimated that 214 million people worldwide have crossed international borders for different reasons (El-Khatib *et al*., 2013). There are approximately 700 refugee camp locations all over the world (UNHCR.2015)^[[7]](#footnote-7)^. The refugee conflicts are not a contemporary occurrence all over the world, but it is new to Europe and the west where only 14% of the world’s displaced people resides in the developed world (Kingsley, 2015). Most of the world's refugees moved to developing countries 86% (UNHCR, 2016). Integration, repatriation and resettlement are the three reasonable solutions and the ultimate goal that UNHCR trying to achieve for refugees around the world.

**8. Syrian Refugees in Jordan:**

Jordan and Syria are bordering countries, with the population that speak the same language and share the same religion. Syria has a larger area and bigger total population; the total population of Jordan is 6 million and 675 thousands^[[8]](#footnote-8)^, while that of Syria is 22 million and 712 thousands^[[9]](#footnote-9)^ (World Health Organization).

Syria has become the great tragedy of this century”, says UN High Commissioner for Refugees (António Guterres). The story has begun since the crises and instability started in Syria (March 2011), where it was assessed that more than half of the 22 million Syrian population had fled their homes, of which almost 4 million people have fled seeking refuge outside Syria in neighboring countries^[[10]](#footnote-10)^. Among these countries are Lebanon, Iraq, Turkey and Jordan (Achilli, 2015). Less than 6% of the Syrian refugees had applied for asylum in Europe (Kingsley, 2015). Nowadays, Syria had become the world’s top source country of refugees with an average of almost one Syrian out of every four refugees**^[[11]](#footnote-11)^.**

Jordan has received an enormous number of Syrian refugees coming from right across the border, from the city of Deraa into northern Jordan through the towns of Jabir and Ramtha^[[12]](#footnote-12)^. With time, the situation became hypercritical as the war aggravated; an average of 1000 Syrian people began to cross the border every day^[[13]](#footnote-13)^. To overcome this high number of refugees fleeing to Jordan, many camps were established in the country^[[14]](#footnote-14)^. These camps are called Za’atari, Marjeeb al-Fahood, Cyber City and Al-Azraq camps. Za’atari refugee camp was the first that set up in July 2012 in a windswept desert. The United Nations had registered 637,859 refugees in Jordan, with over 80,000 registered in the Za’atri camp in February 2015^[[15]](#footnote-15)^. This meant that 80% of Syrian refugees in Jordan settled in urban and rural areas while the remaining 20% lived in the camps^[[16]](#footnote-16)^. The international statistics declared that 41% of the incoming refugees are children, 30% are women and 29% are men (Al-Kilani, 2014). UNHCR’s Home Visits Program Report has estimated that the largest number of Syrian refugees in Jordan are living outside these camps (84%); with approximately (33.6%) living in Amman, (28.4%) in Irbid, (13.2%) in Mafraq and (10.5%) in Zarqa^[[17]](#footnote-17)^.

Several factors are behind this large influx of Syrian refugees to Jordan such as refugees’ kinship and friendship ties with Jordan, the political stability of the Hashemite Kingdom, and the historically tight cultural and geographical relationship between Syria and Jordan (Achilli, 2015). Furthermore, Jordan has always welcomed generously different population from neighboring countries to its community, with more than 40% of Jordan’s current population arising from other countries such as Palestine (two million) and Iraq (29,000) (Al-Kilani, 2014).

**9. Health situation among the Syrian Refugees in Jordan:**

Refugees all over the world are facing several health-related problems and most of them are not gaining proper medical care, and the situation among Syrian refugees is not any different (Burgess, 2004; Pfortmueller *et al*., 2016). The load on the health system is huge in Jordan due to receiving the largest number of Syrian refugees (Arie, 2015).

In Jordan, UNHCR and other partners with the effort of the Jordanian Ministry of Health (MOH) provided health and humanitarian support for Syrian refugees that living inside and outside the camps (Murshidi *et al*., 2013). However, the larger fraction of refugees that lives outside the camps faces different health-related challenges (Ay *et al*., 2016). The needs for this population are not being sufficiently covered (Ay *et al*., 2016; El-Khatib *et al*., 2013). UNHCR-Unregistered refugees must wait for weeks to months for their interview and they need to pay out of pocket for medical services (El-Khatib *et al*., 2013). Since 2012, the Jordanian MOH provided full access to primary and secondary health centers for the Syrians living outside camps along with the local Jordanian population for all UNHCR-registered refugees (Ay *et al*., 2016; Murshidi *et al*., 2013). Once registration expires, refugees can continue to reside in Jordan but they must pay the non-residents fees in the governmental hospitals and centers (except for vaccines) (Ay *et al*., 2016; Murshidi *et al*., 2013). However, governmental health sectors provide urgent care needs only and these sectors are exhausted in many sections such as neonatal incubator, surgical operation, cancer treatment and weapons-related wounds (Murshidi *et al*., 2013; El-Khatib *et al*., 2013). Additionally, some non-governmental organizations and physicians also deliver services to Syrian refugees outside the camps (Doocy *et al*., 2016); Jordan Health AID Society is a popular example for such these organizations. The WHO declared that the number of Syrian refugees getting benefit from public hospitals in Jordan has increased lately by approximately 250% (Coutts & Fouad, 2013). As for those requiring surgical operations outside the refugee camps, such number has increased by 600% ([Coutts](javascript:void(0);) & [Fouad](javascript:void(0);), 2013).

The increasing number of Syrian refugees in Jordan and the subsequent needs for health system accessibility has resulted in a large load on the system (Doocy *et al*., 2016). The Jordanian government is in need for additional assistance to preserve the current level of health access provided to its Syrian refugees (Doocy *et al*., 2016).

The health situation for the Syrian refugees has been studied regarding many conditions such as depression, anxiety and chronic diseases (Basheti et al., 2015; Hassan *et al*., 2016; Doocy *et al*., 2016). A survey involving 1550 Syrian household refugees that conducted in 2014 in Jordan showed that 43.4% of Syrian household members have one or more of the chronic diseases such as cardiovascular disease, hypertension, arthritis, diabetes or respiratory disease^[[18]](#footnote-18)^. Moreover, it has been obtained that more than 26% of this population stopped taking their medicines for longer than two weeks due to high cost^[[19]](#footnote-19)^. More than one study has revealed that the Syrian refugees in Jordan have suffered from psychological distresses such as depression (Gammouh *et al*., 2015; Basheti *et al*., 2015).

Our humanitarian and medical role as pharmacists requires us to make an urgent intervention for the Syrian refugees that became a crucial denomination of Jordanian populations. The MMR service would be an ideal service to deliver to the Syrian refugees in Jordan for the many benefits it showed with other population. MMR in Jordan involving the Syrian refugees have to be one of the essential issues to be tackled in the pharmaceutical research at this stage. This research is going to address the impact of identifying and resolving TRPs by MMR service on many different aspects of the Syrian refugees' health outcomes. In Jordan, such a vital service does not even exist yet, highlighting the importance of conducting MMR studies in the country. Positive results anticipated from such studies would hopefully result in a similar successful service to be implemented one day.

**Methodology**:

**1. Research Hypothesis**

*Null hypothesis*: The implementation of the MMR service for adult Syrian refugees with chronic conditions in Jordan will have no impact on the number of identified TRPs, anxiety scale, self-reported adherence and quality of life in comparison to patients that will not receive this service.

*Alternative hypothesis:* The implementation of the MMR service for adult Syrian refugees with chronic conditions in Jordan will have significant impact on the number of identified TRPs, anxiety scale, self-reported adherence and quality of life in comparison to patients that will not receive this service.

**2. Ethics Approval**

Ethics approval will be obtained from The Jordanian Ministry of Health before starting the clinical work.

**3. Study Design and Clinical Setting**

The study will be conducted over 6 months from May 2016 to October 2016 in three big cities in Jordan (Amman, Mafraq, Zarqa); on Syrian refugees that reside in these two areas. The study will follow the single-blinded randomized controlled trial. Eligible patients will be randomized into two groups, intervention and control. Predetermined randomization number list which will be designed through computer-generated randomization program will be available before starting the study. The patients will be invited to participate in the study and he/she will be asked to sign the informed consent form. Only Syrian refugees who meet all of the following inclusion criteria will be recruited into the study: (1) Living in Jordan for more than six months and intending to stay for the study period which is six months. (2) Being above the age of 18 years. (3) Having at least one chronic condition or taking 5 or more medications or taking more than 12 doses of medication per day. The Exclusion criteria for this study will include: (1) Patients with cognitive or sensory impairment that may prevent conducting the interview. (2) Patients who are planning to travel within the next six months after the baseline home-visit. (3) Patients who are not capable of reading or writing Arabic.

**4. Study Protocol:** Figure (1) shows the concert for the study protocol

Patients Eligibility: patients that meet the recruitment criteria will be invited to participate in the study

The patients will be interviewed at their homes to collect all needed information. The patients will be asked to answer the self-completion questionnaires (Quality of life, scale of anxiety, knowledge of medication, adherence)

Pharmacist counseling will be conducted for intervention group only

The pharmacist will interview the patients 2-3 months post baseline

The patients in intervention group will be asked to visit the physician to confirm these changes

The approved recommendations for control group patients will be kept until the end of the study

The physician will approve part of the recommendations

A report will be written for the physician

The pharmacist will conduct the medication review for all patients

Control group

Intervention group

Randomization

Eligible patients who will fulfill the including criteria will be randomized into two groups, intervention and control groups. Patients will be informed on the nature of the study and will be asked to sign informed consent form. Patients in both intervention and control groups will be interviewed at their homes to assess their use of the treatment and to collect all relevant information. In addition, they will be asked to answer the quality of life questionnaire, the self-reported adherence questionnaire, knowledge about medication questionnaire and the scale of anxiety questionnaire. Medication review (explained in the next section [5]) will be conducted for both intervention and control groups. Only patients in intervention group will receive counseling that does not exceed the clinical pharmacist role (explained in the next section [6]). This will be followed by writing a report to the physician with the findings and recommendations. The report will be delivered to the physician directly with references supported by current guidelines. The physician will tick the recommendations approved and return to the researcher, allowing the clinical pharmacist to convey the approved changes to the patient. The patients will be asked to visit their physician for confirmation of changes. Patients in the active and the control group will be interviewed 2-3 months post baseline, assessing changes in treatment, number of treatment related problems, changes in the quality of life, changes in self-reported adherence, changes in anxiety level and changes in patients’ knowledge about their medication. Patients in the intervention group will provide their perspective of MMR service (role of the pharmacist, value of the service they received, and willingness to pay for such services).

As for the control group, home interview will also be conducted, but no intervention (patient counseling or returning the physician's report) will be done until the end of the study. Questions from control group patients will be recorded and answered at the end of the study. The recommendations that approved by the physician concerning the control group will be returned back to them directly after the study period finished. The pharmacist will ask the patients in the control group to visit the physician to confirm these changes. Patients in control group with life-threatening TRPs will be excluded from the study (serious drug-drug interactions, medication high dose that may damage kidney or liver function over time, serious drug-disease interaction, pregnancy-related problems (including mother and fetus), occurrence of sudden health episode or complication during the study period (Carolan *et al*., 2016)).

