**6. Pharmacist’s Role in Medication Review**

The pharmacist will provide proper education and counseling for patients regarding their illnesses and medications. In addition, information about the importance of adherence to the therapy will be provided to the patients. Advices regarding self-treatment and herbal remedies abuse will be explained to the patients. Effective, open-ended questioning and active listening will be used in order to achieve proper education for the patients. A patient will learn best by hearing spoken instructions and by directly handling medications.

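### Nothing in the eligibility criteria or the randomisation stops two members of one household from entering opposite arms, so controls could receive part of the counselling withheld from them

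*Protocol*

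**What the plan says.** Methodology section 3 sets eligibility: "Only Syrian refugees who meet all of the following inclusion criteria will be recruited into the study". The inclusion criteria cover length of stay in Jordan, age, and disease or medication burden. The last of these is broad: "Having at least one chronic condition or taking 5 or more medications or taking more than 12 doses of medication per day". The three exclusions cover impairment that prevents an interview, travel plans and literacy ("Patients who are not capable of reading or writing Arabic"). None mentions a co-resident who is already enrolled.

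The unit of allocation is the patient: "Eligible patients will be randomized into two groups, intervention and control". The list is fixed in advance ("Predetermined randomization number list which will be designed through computer-generated randomization program will be available before starting the study"), and no household rule is attached to it.

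Sections 4 and 5 place the interview and the medication review in the home for both arms. Section 4 gives counselling to the intervention arm only. For controls, "no intervention (patient counseling or returning the physician's report) will be done until the end of the study", and even their questions are held over for later answer. Section 6 describes the counselling as spoken education on illness, medicines and adherence, and adds: "Advices regarding self-treatment and herbal remedies abuse will be explained to the patients".

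**The concern.** The contrast between arms is partly information, and that information is delivered where people live. If two eligible relatives are both enrolled, individual randomisation can put one in each arm. The control member then shares a home with someone who has been taught about adherence, self-medication and herbal products. Much of that teaching is not specific to the patient who received it.

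Section 4 goes as far as deferring answers to controls' questions, so the protocol itself treats information reaching controls as something to prevent. A split household is a route that it leaves open. The outcomes exposed are self-reported adherence, medication knowledge, and the TRPs that Appendix 6 classes as inappropriate knowledge or inappropriate adherence. The error runs in one direction, toward no difference, and cannot be undone once such pairs have been allocated. Eligibility and the unit of randomisation belong in the protocol, so this is not a matter for a separate analysis plan.

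**Working it through.** **The plan's own figures.** Section 16 gives a difference of 1 TRP, an SD of the change of 2.92, 5% significance, 80% power and 138 patients. It does not say whether 138 is a total or per arm, and it makes no allowance for contamination. Two-sided testing and 1:1 allocation are assumed here.

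- A one-group pre-post t-test needs 68.9, rounded up to 69, and 2 × 69 = 138. This matches exactly.
- A two-group comparison by the normal approximation needs 2 × (1.960 + 0.842)² × 2.92² / 1² = 133.8, so 134 per arm or 268 in total. The figure 138 is close to this only if it is per arm.

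The household point does not depend on which reading is right. Both are carried below.

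**Step 1: share of controls exposed.** Let p be the share of participants enrolled as household pairs. Under independent 1:1 allocation, a control who belongs to a pair has a one-half chance that the other member is in the intervention arm. Exposed controls are therefore p/2. A blocked list would shift the one-half somewhat.

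**Step 2: dilution.** Let c be the share of the intervention effect that passes to an exposed control. Then:

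dilution = (p/2) × c, and observed difference = 1.0 × (1 − (p/2) × c).

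Neither p nor c is in the documents. The assumed ranges are p = 10–30% and c = 10–50%.

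| p | c | Exposed controls | Dilution | Observed difference |
|---|---|---|---|---|
| 10% | 10% | 5% | 0.05 × 0.10 = 0.5% | 0.995 |
| 30% | 50% | 15% | 0.15 × 0.50 = 7.5% | 0.925 |

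**Step 3: what it does to the comparison.** The required size scales with 1/difference².

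- At 0.995: 133.8 / 0.990 = 135.2, so 136 per arm.
- At 0.925: 133.8 / 0.8556 = 156.4, so 157 per arm.
- Power at 0.925 against 1.0: about 46% against 52% if 138 is the total (69 per arm), or about 75% against 81% if 138 is per arm.

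**Step 4: what can pass between relatives.** General advice can. The intervention arm also gets a report on the individual patient, changes approved by a physician and a visit to confirm them (section 4), and these largely cannot pass. Section 13 names eight TRP types. Non-adherence is clearly open to shared advice, and unnecessary drug use perhaps is. Knowledge problems are counted in Appendix 6 but are not named in section 13. This is why c is capped well below 1 for the TRP count. For adherence and knowledge as separate outcomes, c could be higher than for TRPs.

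**The case against.** The strongest reply is that nothing shows co-residents will be enrolled. Section 3 says that patients who meet the criteria are invited; it does not describe screening other people in the home. The patient record in Appendix 5 has a field for the clinic, and section 14 says refugees attend different physicians and organisations, so recruitment may run through clinics. No section says that relatives sit in on the counselling, and that counselling happens at the home visit is itself inferred from sections 4 to 6. All of this stands, and it is why the point is conditional.

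A reader might infer from the Literature Review, section 9 ("43.4% of Syrian household members have one or more of the chronic diseases"), that a visited home will usually hold a second eligible adult. The text does not support that. It does not settle whether the figure is a share of individuals or of households with an affected member, nor whether it is confined to adults. Having a chronic disease is also not the same as being eligible: literacy, residence, travel plans and consent all narrow the field. The figure makes a second eligible adult plausible and no more.

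A reader might also infer that most or all of the effect could leak, or that a split household nullifies the control condition. Patient-specific, physician-approved changes largely stay with the patient, so full transfer is not a realistic bound for the TRP count.

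What survives is the structural gap: the criteria allow split households and no other provision prevents them.

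**Conclusion.** The gap is real and its effect is conditional. As written, the protocol permits co-residents in opposite arms, reviews medication in the home and counsels one arm only. If such pairs are enrolled, the adherence and knowledge outcomes, and the adherence and knowledge part of the TRP count, would be biased toward no difference.

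On the assumed ranges the loss is between negligible and modest: 0.5–7.5% of the TRP effect, and at most about six percentage points of power under either reading of 138. This rests on assumed values of p and c, 1:1 allocation, two-sided testing and counselling given at the home visit. The documents do not support saying that the effect will be diluted, only that it could be. Severity is low; the case for acting is that prevention is cheap and repair after allocation is not possible.

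**What to change.** Add to the criteria in section 3: *one participant per household; where more than one eligible member is willing, one is chosen at random before allocation*. This closes the route within the home and also removes correlation between co-residents from the analysis.

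The cost is brief screening of other willing members before allocation and somewhat more homes to visit for the same number of patients. The required sample size does not change.

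Giving later household members the arm already drawn for the first is not a good substitute. Their allocation would be known before they were invited and consented, which breaks concealment.

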**8. Follow-up Assessments**

Both groups will be revisited at their homes 2-3 months after the baseline assessment. This assessment traces changes in treatment, number and type of TRPs, adherence, anxiety, quality of life and patients’ knowledge about medication (Figure 1). A collective report highlighting the feasibility and success of the study will be submit to the involved physicians three months following the end of the study.

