**15. physicians’ approval rate of the Pharmacist Recommendations**

After the medication review, all the pharmacist’s recommendations will be sent to the physicians to take the approval from them. The physicians will approve some of these recommendations. To calculate the approval rate for the pharmacist recommendation, the total number of approved recommendations by physicians will be divided by the total number of all recommendations (approved + rejected) sent to the physicians.

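### Control patients' approved recommendations are held to the end of the six-month study rather than to their own last visit at 2-3 months, a further wait of up to 3-4 months that protects no later measurement in that patient

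*Protocol*

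**What the plan says.** Section 3 fixes the calendar: "The study will be conducted over 6 months from May 2016 to October 2016". The first inclusion criterion repeats the length, requiring patients to be "intending to stay for the study period which is six months".

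Section 4 gives three release points for the control arm, all tied to the study and none to the patient:

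- Figure 1: "The approved recommendations for control group patients will be kept until the end of the study".
- Control-group text, on recommendations: "The recommendations that approved by the physician concerning the control group will be returned back to them directly after the study period finished".
- Control-group text, on patients' questions: "Questions from control group patients will be recorded and answered at the end of the study".

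On release, a further step follows: "The pharmacist will ask the patients in the control group to visit the physician to confirm these changes". Counselling of controls is likewise withheld to the end of the study.

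Section 8 sets the last measurement: "Both groups will be revisited at their homes 2-3 months after the baseline assessment". The patient form in Appendix 5 provides for a first and a second interview only.

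**The concern.** Withholding the service from controls until their outcomes are recorded is what makes the comparison possible. Once the second interview is done, that reason is gone for that patient. The protocol nevertheless keeps approved corrections and answers to questions back to a study-level date, which can be months later.

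The stake is patient protection. Going by the classification in Appendix 6, what is held can include untreated conditions, a safer or more effective drug, poor adherence and poor understanding of the medicines. There is also a practical gap. Return after the study period requires the pharmacist to contact each control again, hand over recommendations, answer questions and ask for a physician visit. The protocol schedules no such contact.

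**Working it through.** **Inputs**

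- Study period: May to October 2016 inclusive, 6 months (Section 3). May, June, July, August, September and October make 6, so the stated length agrees with the stated dates.
- Last outcome visit: F = 2 to 3 months after baseline (Sections 4 and 8).
- Enrolment time: e months after 1 May 2016. The protocol does not give it, so it is varied.
- Recruitment length: R months. Not stated; assumed uniform from 1 May where a mean is needed.

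**Wait after the last visit, calendar reading**

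Wait = 6 − e − F.

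| Enrolled at month e | Visit at 2 months | Visit at 3 months |
|---|---|---|
| 0 | 4 | 3 |
| 1 | 3 | 2 |
| 2 | 2 | 1 |
| 3 | 1 | 0 |
| 4 | 0 | not feasible |

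In days, for enrolment on 1 May:

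- Visit on 1 July: 30 + 31 + 30 + 31 = 122 days to 31 October.
- Visit on 1 August: 30 + 30 + 31 = 91 days to 31 October.

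**Mean wait under uniform recruitment**

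Mean enrolment time is R/2, so mean wait = 6 − F − R/2.

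| Assumed R | F = 2 | F = 3 |
|---|---|---|
| Last feasible (R = 6 − F) | 6 − 2 − 2 = 2.0 months | 6 − 3 − 1.5 = 1.5 months |
| 2 months | 6 − 2 − 1 = 3.0 months | 6 − 3 − 1 = 2.0 months |
| 1 month | 6 − 2 − 0.5 = 3.5 months | 6 − 3 − 0.5 = 2.5 months |

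The rows for 1 and 2 months show sensitivity only. Nothing in the protocol says recruitment was planned to be that short.

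**Other readings**

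- Six months counted from each patient's own baseline. The exclusion of patients planning to travel within six months of the baseline visit fits this. Every control then waits 6 − 3 = 3 to 6 − 2 = 4 months.
- The study ends for each patient at the second interview. The wait is zero.

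**Which reading the text supports**

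Elsewhere the protocol uses the end of the study for trial-level events. Section 14 computes physician acceptance at that point over all contacted physicians, and Section 8 times a collective report three months after it. Where the protocol means the patient's own visit, it gives the interval of 2-3 months from baseline. The zero-wait reading is possible but goes against this usage.

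**The case against.** The case on the other side has five parts.

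- **The wording is loose.** Figure 1 shows no patient step after the 2-3 month interview, the form has only two interviews, and the recommendations are to go back directly. This could mean release at the second interview. It stands as a possibility, but the six-month definition and the usage in Sections 8 and 14 point the other way. If both readings are open, the protocol should still say which applies.
- **Four months is a ceiling.** This stands. On the calendar reading it applies only to a control enrolled on the first day and revisited at exactly 2 months.
- **The harm is limited by other provisions.** This also stands. Section 4 excludes controls with life-threatening problems and defines them broadly, down to doses that may damage the kidney or liver over time. Under Section 15 the pharmacist's "recommendations will be sent to the physicians to take the approval from them", so the physician knows of them and nothing bars action. What can be delayed is the patient's own receipt of non-life-threatening corrections and of answers to questions.
- **A common release date guards against contamination.** Released controls might talk to controls not yet assessed, and adherence and knowledge are self-reported or directly taught. The risk is real but incremental: intervention patients in the same cities are counselled from baseline, so such contact is already possible. The protocol does not offer this as its reason.
- **Recommendations approved 2-3 months earlier may be out of date at the second visit.** They may, but they would be older still at the end of the study.

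The point has no bearing on the primary outcome, sample size or analysis, because any delay falls after the patient's last measurement.

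**Conclusion.** The concern holds. On the plain reading, approved corrections for controls are held past the last measurement by 0 to 4 months: at most 122 days after a 2-month visit and 91 days after a 3-month visit, and about 1.5 to 2 months on average if recruitment is uniform up to the last feasible date. If the six months run from each patient's baseline, the wait is 3 to 4 months for every control. If the end of the study means the patient's second interview, it is zero, but the text does not say so.

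This is a bounded patient-protection matter that should be fixed. It is not a threat to validity. The averages depend on a recruitment pattern that the protocol does not state.

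**What to change.** In Section 4, including Figure 1, replace each reference to the end of the study or of the study period as the control arm's release point with completion of the patient's own 2-3 month follow-up assessment. At the end of that home visit, once the questionnaires and the information for the count of treatment-related problems have been recorded, the pharmacist returns the approved recommendations, answers the recorded questions and asks the patient to see the physician.

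The change is one of wording. No extra visit is needed, since the pharmacist is already in the home, although the visit will take somewhat longer. No outcome data are lost for that patient, because nothing is collected afterwards. The longest hold from baseline falls from 6 months to 2-3 months. The cost is the small added risk that released controls speak to controls still awaiting assessment.
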